Starting from these premises, it is necessary to develop an intervention to investigate people’s psychosocial conditions and reduce possible psychophysiological activation; due to the current circumstances, such an intervention must be internet-based.

Previous studies demonstrated that interventions based on natural sounds, respiration, and meditation may help individuals to alleviate the effects of stress by reducing physiological arousal and restoring autonomic balance [11-14]. In fact, listening to natural sounds significantly reduces human stress processes [13,15]. On the other hand, guided relaxation techniques are widely used to produce a deep state of relaxation and enhance physical and emotional well-being. Deep breathing exercises and focusing attention on body perception are two of the main techniques used to reduce hyperarousal and achieve a more relaxed condition. Deep breathing can be also defined as “an efficient integrative body-mind training for dealing with stress, anxiety and psychosomatic conditions” [16]; it may help people to slow their breathing, take in more oxygen, and reduce the use of their shoulder, neck, and upper chest muscles, thus achieving better emotional balance and social adaptation [17]. On the other hand, body scan meditation aims to focus attention on different parts of the body and help people become aware of their bodily sensations, such as pain, tension, warmth, or relaxation [18,19]. We chose to employ these two techniques because they involve different cognitive and psychophysiological processes. In the present study protocol, we aim to test and compare the efficacy of natural sounds, breathing regulation, and body scan meditation to assess which intervention is the most effective for the target population. Applying these interventions to people forced into mandatory social isolation may help them become more aware of their mind-body condition and reduce negative effects. Moreover, scientific studies have shown that online relaxation techniques as well as in-person programs achieve significant results; these findings may support the implementation of remote interventions, which are currently a necessary feature of proposed programs [20,21]. However, a comparison of natural sounds, respiration, and body scan meditation techniques in internet-based interventions is still lacking in the literature.

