### Data Analysis

Group differences in demographic data and pretreatment measures will be analyzed with one-way analysis of variance (ANOVA) followed by *t* tests with Bonferroni corrected *P* values and chi-square tests. Differences in questionnaire scores (ie, STAI-Y, ASI-3, BVS) between groups will be examined using the same analysis. STAI scores will also be compared to clinical cutoffs. The internal consistency of the scales (Cronbach α) in our sample will also be assessed.

As the main aim of this study is to test the difference in efficacy between audio clips, our main analysis will be one-way ANOVA on gain relaxation scores [30], with 3 groups and fixed effects and with no interaction. According to our main objective, we performed a priori sample size calculation, considering a 0.25 effect size on the level of relaxation, with a high statistical power (0.95) and an alpha of .05. Considering the specified values, we will need a total sample size of 252 participants with complete surveys to reach the desired statistical power (84 per group). In view of the possibility of attrition of participants, which may occur in the present electronic health (eHealth) trial in the form of incomplete questionnaires or dropout before listening to the complete audio clips, we estimate that we will obtain incomplete data for 30% of the participants who will start the survey by clicking on the link and who will not continue with the questionnaires; thus, we should register a total of 328 participants.

Independent sample *t* tests of the relaxation level between paired groups will also be carried out on participants who will complete the entire survey (eg, without considering participants who dropped out before the randomized exposure to the audio clips).

The same analysis will be conducted for the participants’ perceived stress and fear related to COVID-19 thoughts, assessed with the VAS continuous scale, and for their emotional states, measured through the SAM. The between-group post-exercise Hedges g effect size (CI 95%) will be computed. As the randomization will be automatically performed by Qualtrics, the researchers who analyze the data will be blinded to which audio clip participants received.

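### Efficacy t tests between pairs of clips are run on six outcomes with no stated gate or correction, although Bonferroni is specified at baseline: about 12% chance of at least one false pairwise difference on relaxation, more over all six

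*Protocol article*

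**What the plan says.** All statistical statements are in the protocol article, Methods, Data Analysis, unless another section is named.

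- **Main analysis.** The text states that "our main analysis will be one-way ANOVA on gain relaxation scores". The sample size rests on this test, "considering a 0.25 effect size on the level of relaxation", "with a high statistical power (0.95) and an alpha of .05", and comes to 252 completers, 84 per group.
- **Pairwise tests on efficacy.** Independent-sample t "tests of the relaxation level between paired groups will also be carried out". Nothing makes them depend on the ANOVA result, and no adjustment of their P values is given.
- **Other outcomes.** The same analysis is extended to stress and COVID-19 fear, "assessed with the VAS continuous scale, and for their emotional states, measured through the SAM". Measures and Design lists three SAM items, so there are six outcomes with relaxation. Only the later covariate analyses are called explorative.
- **Baseline comparisons.** Here the ANOVA is followed by t "tests with Bonferroni corrected" P values. The trait anxiety, anxiety sensitivity and body vigilance questionnaires, completed before randomization, are handled in the same way.
- **Aims.** Background says the three practices are compared "to assess which intervention is the most effective for the target population". Objective and Results predict that the guided practices will do better than natural sounds.

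**The concern.** An omnibus ANOVA shows that the three groups differ somewhere, not which clip differs from which. The predicted advantage of guided practices over natural sounds, and any ranking of the clips, has to be read from pairwise comparisons. The .05 in the sample size calculation covers only the omnibus relaxation test.

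The article does control multiplicity, but in the less useful place. Baseline differences between randomized groups can only arise by chance, and no efficacy conclusion depends on them. The efficacy comparisons that carry the stated hypotheses get no stated protection and are repeated over six outcomes. Followed as written, an isolated P value below .05 for one pair on one outcome could be reported as a difference between clips when none exists.

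**Working it through.** **Inputs.** From the article: 3 groups, 84 completers per group, alpha .05, power 0.95, effect size 0.25, six outcomes. Assumed: two-sided t tests (sidedness is not stated), t tests on the same type of score as the ANOVA, normal outcomes, and equal correlation between outcomes. The article gives no correlations, so a range is used.

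**1. Reproduce the plan's sample size.** Read 0.25 as Cohen's f. The noncentrality is N × f² = 252 × 0.0625 = 15.75, with 2 and 249 degrees of freedom. The noncentral F distribution gives power 0.9515. The smallest N divisible by 3 that reaches 0.95 is 252, so the stated figure reproduces. It concerns the omnibus relaxation test only.

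**2. Count the tests.** Three groups give 3 pairs. Six outcomes give 6 omnibus tests and 6 × 3 = 18 pairwise tests.

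**3. Error on relaxation, no true differences.** With a pooled variance, the chance that at least one of the three t tests is significant is

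1 − P(Q ≤ √2 × t₀.₉₇₅,₂₄₉), where Q is the studentized range for 3 groups and 249 df.

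Here √2 × 1.9695 = 2.785, and the result is 0.122. Simulation with two-group variances gave 0.119 to 0.126. Treating the three tests as independent would give 1 − 0.95³ = 0.143, which is too high because the pairs share groups.

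**4. Error over six outcomes, no true differences.** Simulation, 3 × 84 participants, 20,000 runs per correlation, simulation error about 0.35 percentage points:

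| Assumed correlation | At least one of 18 pairwise tests | At least one of 6 ANOVAs | One clip beats both others on some outcome |
|---|---|---|---|
| 0 | 55.0% | 27.0% | 8.1% |
| 0.3 | 50.6% | 24.9% | 8.1% |
| 0.5 | 43.6% | 21.2% | 6.9% |
| 0.7 | 35.7% | 17.0% | 5.7% |
| 0.8 | 31.1% | 14.5% | 5.0% |

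Check at correlation 0: 1 − (1 − 0.122)⁶ = 0.54, in line with the simulated 55%. On relaxation alone, one clip falsely beats both others in about 1.5% of trials.

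**5. Effect of gating.**

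- t tests read only after that outcome's ANOVA has P < .05: 5% on relaxation, and about 27% to 15% over six outcomes (correlation 0 to 0.8).
- The same, with the relaxation ANOVA also as gatekeeper for the other five outcomes: about 5% overall when no outcome has a true difference.

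**6. Why the gate suffices for relaxation.** If all three means are equal, a false claim needs a significant ANOVA, which has probability 5%. If one clip differs from two equal ones, only one pair is truly null, and its t test has error 5%. If all three differ, no false difference can be declared. The familywise error is therefore at most 5% in every case.

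**The case against.** **The main analysis is intact.** A reader might infer that the trial's primary error rate is inflated. It is not: one ANOVA is named as main, the trial is sized for it, and it keeps 5%. This stands. The inflation concerns only the pairwise and other-outcome conclusions.

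**The figures are not the chance of a spurious winner.** It is tempting to read 12%, or the six-outcome range, as the chance of wrongly naming a best clip. If that means one clip significantly better than both others, the chance is about 1.5% on relaxation and 5% to 8% over six outcomes. Nor does the article state a rule by which a winner would be declared. This stands too. The lesser error still matters, because the prediction of guided practice over natural sounds is a two-clip comparison, and one false difference could be taken as support for it.

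**Silence is not refusal.** The article is condensed, an analysis plan may exist, and a further test being carried out does not exclude using it as follow-up to the ANOVA. This stands in part: the fair statement is that no gate or correction is stated. But the same section specifies a follow-up sequence with Bonferroni at baseline and a different arrangement for efficacy. That is a choice on the page, not only omitted detail.

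**Treating all 18 tests as one family is debatable.** Only relaxation is called main and powered, so the rest might be taken as secondary. On that view 12% is the relevant figure. If only the two guided-versus-natural contrasts were tested, the rate would be at most 1 − 0.95² = 9.75%. But the article runs all pairs, does not label the other five outcomes, and states its prediction across them.

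**Zero correlation is implausible** for items such as relaxation and stress rated at the same moment. Agreed: 55% is the upper end of an assumed range, not an estimate.

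**Conclusion.** The point holds in limited form and should be corrected. Followed as written, the chance of at least one false pairwise difference on relaxation is about 12% instead of 5%; this figure needs no assumption about correlations. The six-outcome figure, about 55% to 31%, depends on assumed correlations of 0 to 0.8 and on counting all 18 pairwise tests together. Both figures apply when no clip differs from any other. The weakness lies in the protection of the between-clip claims that the article sets out to make.

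**What to change.** 1. State that the pairwise tests on relaxation are interpreted only if the three-group relaxation ANOVA is significant at .05. With three groups no further correction is needed.
2. Label stress, COVID-19 fear and the three SAM items secondary or exploratory, with no confirmatory claim. Alternatively, test them confirmatorily only after a significant relaxation ANOVA, with a multiplicity correction that covers their pairwise tests as well as their group tests. Correcting the five group tests alone is not enough: if one clip truly differs on all five outcomes, one null pair remains on each, and uncorrected t tests on independent outcomes would err in up to 1 − 0.95⁵ = 23% of trials. A separate 5% family for these outcomes, beside the 5% relaxation family, would also allow up to about 10% overall.

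The baseline tests need no change for this purpose; they do not affect the efficacy error rate.

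**Cost.** Wording only. The main test keeps its power of 0.95 at 252 completers. Pairwise and secondary claims lose a little power.

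### The main test is on gain scores but the reported Hedges g is on unadjusted post-exercise scores, so the effect size and its CI are not those of the primary test

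*Protocol article*

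**What the plan says.** All the relevant text is in the protocol article, Data Analysis.

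- **Main test:** "our main analysis will be one-way ANOVA on gain relaxation scores [30], with 3 groups and fixed effects and with no interaction".
- **Sample size:** it is calculated "considering a 0.25 effect size on the level of relaxation", "with a high statistical power (0.95) and an alpha of .05", giving 252 complete surveys, 84 per group.
- **Pairwise follow-up:** independent-sample t "tests of the relaxation level between paired groups will also be carried out". The sentence does not say whether the score compared is the gain or the post-exercise rating.
- **Effect size:** "The between-group post-exercise Hedges g effect size (CI 95%) will be computed". This one names its variable explicitly. No effect size on gain is mentioned.
- **Scope:** the same analysis is to be applied to stress, COVID-19-related fear and the SAM ratings. Measures and Design says that all of these are rated before and after the audio, so each outcome has a baseline value.
- **Baseline:** group differences in pretreatment measures will be tested, but no consequence for the main analysis or for g follows from that.

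**The concern.** The test and the effect size answer the same question with different variables. The ANOVA asks whether the arms differ in change; g describes how far apart they are at the end, with no account taken of where they started. A reader of the results would naturally take g and its 95% CI as the size of the effect just tested. As planned they are not, and the two can point different ways.

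This matters because the Discussion promises to say whether one clip does better than the others and by how much. The between-group g is the only planned measure of how much. The mismatch can recur over three pairs of arms and every pre-post outcome.

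**Working it through.** **Inputs.** From the protocol article: three arms, 84 per arm, effect size 0.25, alpha .05, power 0.95, every outcome rated before and after. Not given, so assumed: pre-post correlation ρ from 0.3 to 0.7, and equal SD before and after (results in units of that SD).

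**1. The plan's own figure.** Power of a one-way fixed-effects ANOVA with k = 3, reading 0.25 as Cohen's f, noncentrality N × 0.25²:
- N = 249: power 0.949
- N = 252: power 0.951

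The smallest balanced N is 252, as stated. The sample size is not in question here.

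**2. Gap between the two measures, raw units.** For arms A and B:

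(post_A − post_B) − (gain_A − gain_B) = pre_A − pre_B

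This is an identity. At 84 per arm the baseline difference has:
- SE = √(2/84) = 0.154 SD
- 95% chance range = ±1.96 × 0.154 = ±0.30 SD
- mean absolute value = 0.154 × √(2/π) = 0.12 SD

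**3. Extra gap on the g scale.** SD_gain / SD_post = √(2(1 − ρ)):
- ρ = 0.3: 1.18
- ρ = 0.5: 1.00
- ρ = 0.7: 0.77

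So even with identical baselines, a g standardised by the gain SD and one standardised by the post-exercise SD agree only near ρ = 0.5.

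**4. How often the two disagree.** Simulated arm-mean differences for one pair (bivariate normal, 84 per arm, critical value 1.96), comparing the gain contrast with the 95% CI of the post-exercise difference. The values 0.3 and 0.53 are illustrations in post-exercise SDs. The second comes from f = 0.25 if both guided clips beat natural sounds equally: 0.25 × 3/√2 = 0.53.

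| True difference | ρ = 0.3 | ρ = 0.5 | ρ = 0.7 |
|---|---|---|---|
| 0.3 SD: opposite sides of significance | 31% | 33% | 40% |
| 0.53 SD: opposite sides of significance | 16% | 10% | 7% |
| 0: point estimates of opposite sign | 30% | 33% | 37% |

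These rates are for a pairwise gain contrast, not the three-arm F test.

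**5. Precision of the options.** Variance of a between-arm difference, relative to the post-score variance: post score 1; gain 2(1 − ρ); ANCOVA 1 − ρ².
- ρ = 0.3: 1, 1.40, 0.91
- ρ = 0.5: 1, 1.00, 0.75
- ρ = 0.7: 1, 0.60, 0.51

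ANCOVA is never worse than gain, since 2(1 − ρ) − (1 − ρ²) = (1 − ρ)² ≥ 0. It costs one degree of freedom. Gain beats the post score only when ρ exceeds 0.5.

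**The case against.** Several points on the other side stand, and they limit the finding.

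- **No bias.** Arms are randomised, so the post-exercise difference and the gain difference estimate the same raw effect. An unadjusted post-exercise g is a valid estimate. A reader might infer that g is biased; the documents do not support that. The planned baseline comparison would also make any gap visible.
- **The pairwise tests may be on gain.** A reader might infer that they use post-exercise scores. But the sample-size sentence uses similar wording, "considering a 0.25 effect size on the level of relaxation", for an ANOVA just defined on gain, and the term is also how the rated item is described. It is probably a loose name for the outcome. Only the ambiguity can be raised.
- **The protocol does not rank g.** It gets one sentence, after the secondary outcomes, and is not called the main estimate. Nothing says that gain means will go unreported.
- **Extreme contradiction is rare.** A significant gain difference beside a post-exercise difference below 0.1 SD occurs in 0.5% to 4.2% of simulated trials at a true 0.3 SD, and in under 0.3% at 0.53 SD. The realistic problem is the two falling on opposite sides of the significance threshold.
- **The gap is not a fixed share of a planned pairwise effect.** The protocol gives 0.25 only. The 0.53 depends on the pattern of means: three evenly spaced means would give 2 × 0.25 × √1.5 = 0.61 for the extreme pair. An effect planned for the gain ANOVA is also in gain SDs, whereas the baseline gap is in baseline SDs.

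What remains is that the protocol states both variables explicitly, and they differ. This is a choice that the article fixes, not a detail left to a fuller document.

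**Conclusion.** The point holds in this limited form. Followed as written, the plan reports a between-group effect size and CI that do not belong to its primary test. The raw discrepancy is the chance baseline difference between arms, typically about 0.12 SD and within ±0.30 SD in 95% of cases at 84 per arm; differing standardisers add to it on the g scale. The consequence is avoidable inconsistency and, relative to a baseline-adjusted analysis, lost precision.

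The identity and the SE rest only on 84 per arm and randomisation. The disagreement rates rest on the assumed correlations, equal SDs and normality. Neither the validity of the gain ANOVA nor the sample size of 252 is affected. The change is worth making because it costs nothing, not because the trial would otherwise mislead.

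**What to change.** State that the main test, the pairwise contrasts and g all come from one analysis, for relaxation and for every other pre-post outcome. Either:

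- **(a)** keep the gain ANOVA, and compute the pairwise tests and g from the gain difference; or
- **(b)** use ANCOVA of the post-exercise score on the baseline score for all three.

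Option (b) is the more precise, but it cures the mismatch only if the main test is changed as well; an ANCOVA-based g beside a gain ANOVA would still not match. In both cases name the standardising SD (for example the pooled baseline SD), give the 95% CI, and report raw post-exercise means descriptively. The pairwise sentence should name its score.

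The cost is wording only. The ratings are already collected and N stays at 252.

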## Results

The expected results are that the audio clips will be effective in reducing the participants’ perceived stress and degree of preoccupation with thoughts related to COVID-19; we also believe that the guided techniques will have a greater effect on relaxation and emotional state enhancement compared to the natural sounds.

The research protocol was approved by the Ethical Committee of the first author’s university on April 30, 2020. Recruitment started in May 2020.

## Discussion

People are confronting the COVID-19 pandemic worldwide. This alarming event and the unknown consequences it will trigger in citizens’ lives have led to increases in stress levels and psychophysiological arousal. Moreover, lockdowns have forced people into social isolation and are preventing the implementation of in-person programs to target psychological issues.

The present randomized study will provide data on the effectiveness of remotely delivered interventions with natural sounds, deep breathing, and meditation practice in improving people’s perceived relaxation, psychomotor activation, level of worries associated with COVID-19, and emotional state; we will also obtain data on people’s experiences with these techniques.

The study will also shed light on whether one of these exercises provides increased benefits compared to the others and if so, to what extent. Indeed, a comparison among natural sounds, respiration, and body scan meditation techniques in internet-based interventions is lacking in the literature.

As a first assessment of the efficacy of these approaches, the present study will have the possible limitation of being a single-session guided intervention. Thus, we will not be able to assess differences in the efficacy of more prolonged exposure to the relaxation sessions. Furthermore, the length of the audio clips may need to be adjusted in future interventions in light of the participants’ reports.

If effective, this study could guide the development of future low-cost remote interventions to reduce worries and anxiety in the general population. Future studies may also assess and compare the efficacy of these approaches in clinical protocols for patients struggling with anxiety and hyperarousal.

## Abbreviations

ASI-3: Anxiety Sensitivity Index-3
BVS: Body Vigilance Scale
COVID-19: coronavirus disease
eHealth: electronic health
SAM: Self-Assessment Manikin
STAI-Y: State-Trait Anxiety Inventory form-trait subscale
VAS: Visual Analogue Scale
